### Control group

The comparator will be routine care. Physicians working in an ED during the control period will manage the patients as they usually do. Physicians are provided with the guidance for CAP from the Swiss Society of Infectious Diseases (SSI) to standardized practices [26]. However, decisions on antibiotics and on the use of diagnostic tests are left to the physicians.

### Training

Before starting the study, ED physicians of all participating centers will receive a 1-h training on the epidemiology and management of CAP in Switzerland based on Swiss guidelines [27] as well as explanations of the rationale of the study.

*In the month prior to the intervention period*, the medical supervisors (senior registrars and senior physicians) of the respective ED will attend a 1-h presentation on the scientific data behind the algorithm. They will perform a 2-h e-learning training on LUS available on the learning platform “PocUS Academy” [32] offering structured teaching on ultrasonography, certified by the Swiss Society of Ultrasonography in Medicine. The respective supervisors will also attend a 1-h theoretical and 2-h practical training (1-h training on image acquisition on healthy volunteers and 1-h training on pneumonia diagnosis on patients admitted with pneumonia) led by an experienced instructor in LUS. This will be based on international recommendations [27, 28] and on the POCUS course of the Swiss Society of Ultrasonography (SGUM). Competencies in LUS will be assessed by an online quiz and a practical test with LUS image acquisition: physicians with previous expertise in LUS will record two examinations for review, while those without prior expertise will record five examinations, as suggested in the literature [33]. This assessment is based on the lung-ultrasound objective structured assessment of technical skills (LUS-OSAUS) [34]. Only physicians who achieved 80% of good quality image acquisition and 80% of correct answers in the online quiz will be allowed to perform LUS during the study. If quality objectives are not achieved, an extra one-to-one 1- to 2-h practical supervision will be offered. If the second test evaluation does not reach learning objective, the physician will not perform LUS in the study. If the objectives of the online quiz are not achieved, the 2-h e-learning will be repeated. If the second test evaluation does not reach learning objective, the physician will not perform LUS in the study.

*During the month after rolling into the intervention*, all recorded LUS (around seven per center) will be reviewed for quality and interpretation by a LUS expert with direct feedback to the physicians. If the quality or interpretation of LUS is insufficient, an extra one-to-one 1- to 2-h practical supervision will be offered to the concerned physicians.

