**Discussion:**

The PLUS algorithm aims to optimize prescription of antibiotics through improved diagnostic performance and maximization of physician adherence, while ensuring safety. It is based on previously validated tests and does therefore not expose participants to unforeseeable risks. Cluster randomization prevents cross-contamination between study groups, as physicians are not exposed to the intervention during or before the control period. The stepped-wedge implementation of the intervention allows effect calculation from both between- and within-cluster comparisons, which enhances statistical power and allows smaller sample size than a parallel cluster design. Moreover, it enables the training of all centers for the intervention, simplifying implementation if the results prove successful.

The PLUS algorithm has the potential to improve the identification of LRTIs that would benefit from antibiotics. When scaled, the expected reduction in the proportion of antibiotics prescribed has the potential to not only decrease side effects and costs but also mitigate antibiotic resistance.

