**Trial status:**

Recruitment started on December 5, 2022, and will be completed on November 3, 2024. Current protocol version is version 3.0, dated April 3, 2023.

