## Methods: Assignment of interventions

### Randomization, allocation, and timeline

The unit of randomization will be the nine centers, representing the clusters. In accordance with the stepped wedge cluster randomization design, after a common baseline 10-week-period of usual care (all patients included in the control group), one center will switch to the intervention phase (patients included in the intervention group) at each pre-determined time period (every 10 weeks, which corresponds to a step). All study centers will be in the intervention period for the last 10 weeks of the study (Table 5). The total duration of the study will be 113 weeks, including the follow-ups. The sequence of rolling into intervention (from control period to intervention period) was randomly generated between study centers using the web-based randomizing program: random.org. The nature of the study intervention precludes randomization at the patients’ level. Indeed, the intervention is targeting the decision-making process of the clinician and might contaminate the usual care group in case of patients’ randomization. Figure 3 represents the CONSORT flow diagram of the PLUS-IS-LESS study following SPIRIT guidance.

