### Quality management and monitoring

#### Monitoring

The monitoring activities are coordinated by the Clinical Research Center (CRC) Lausanne. The Clinical Trial Center Zurich (members of the Swiss Clinical Trial Organization (SCTO) and CTUs Network) is contracted by Lausanne to perform monitoring activities at some local sites.

A risk-adapted monitoring strategy were developed according to the SCTO guidelines (Guidelines for Risk-Based Monitoring, version 3.0). The monitoring strategy (nature and extent of the monitoring activities) were described in a monitoring plan. Site initiation visits were conducted on each site before the start of the trial. Then interim monitoring visits (6 per site) will be performed on site and focusing mainly on safety and patient eligibility. A closeout monitoring visit per study site will be performed at the end of the trial to ensure all pending actions are resolved and study documentation is ready for archival.

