### Analyses

#### Sample size

The study is designed to demonstrate non-inferiority of the intervention in term of clinical failure occurrence and superiority in term of reducing antibiotic prescription. We plan to include 1530 patients in 9 study centers. Every study center will recruit 170 patients over about 2 years.

According to a stepped-wedge cluster-randomized design with a control period plus nine switch periods (steps) and the same number of clusters (one switch to intervention at each step), a mean number of 15 patients per unit and per time period will guarantee a 80% power (one-sided type I error *α* = 0.05) to prove non-inferiority regarding clinical failure (safety), if the proportion of clinical failure is 20% in both groups, with a non-inferiority margin of 10%, and assuming an intra-cluster correlation (ICC) of 0.2 and a coefficient of variation (cv) of the number of patients across units of 0.3. With 15 patients per unit and per time period, we would obtain a total sample size of 1350 (15 × 9 × (9+1)) patients. Further considering a 10% of lost to follow-up, we anticipate 15/0.9 = 17 patients per unit and per time period, leading to our final sample size of 1530 (17 × 9 × (9+1)) patients.

In our calculation, the ICC of 0.2 is based on results of a previous trial, the UltraPro trial [37]. The coefficient of variation of 0.3 in the number of patients between units is intended to allow for some variability between centers in the number of patients recruited. With an average number of 15 patients per cluster and per step, this corresponds to admitting that 95% of the clusters will recruit between 6 and 24 patients per step (between 60 and 240 in total). Correcting for 10% loss to follow-up, the same range will be between 67 and 267.

Of note, the 10% non-inferiority margin is supported by US FDA recommendations for anti-infectious trials assessing clinical success of a new treatment [38]. Sample size calculation with a 5% margin would lead to 5100 patients jeopardizing the feasibility of the trial.

This sample size in the framework of a stepped-wedge design guarantees a power of more than 90% to prove superiority regarding antibiotics prescription (efficacy), if the proportion of antibiotics prescribed is 0.65 in the control group and 0.5 in the intervention group (*α* = 0.05).

The sample size was calculated with R software, based on the manuscripts by Hemming et al. [39] and Harrison et al. [40].

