We expect that there will be some overruling, when antibiotic prescription is not recommended. To decrease the risk of overruling, we presented the rationale behind the algorithm during the site initiation visits. In patients in whom the algorithm is overruled and antibiotics are prescribed in spite of the recommendation of the algorithm, PCT will be repeated after 6–24 h. In case of low PCT levels, it will be recommended to stop antibiotics. A close monitoring will be performed to rapidly detect and correct non-compliance problems.

The PLUS algorithm based on clinical scores and easy-to-use diagnostic tests has the potential to improve the identification of patients with a LRTI who will benefit from antibiotics and reduce unnecessary antibiotic treatments. This diminished prescription of antibiotics will decrease side effects, cost, and resistance which are global health problems. The World Health Organization Trial Registration Data Set for PLUS-IS-LESS study is displayed in Table 7.

**Table 7 Tab7:** World Health Organization Trial Registration Data Set for PLUS-IS-LESS study

Data category	Information
Primary Registry and Trial Identifying Number	www.ClinicalTrials.gov, NCT05463406
Date of Registration in Primary Registry	19 June 2022
Secondary Identifying Numbers	BASEC number 2022-00738
Trial Protocol version	Study protocol V3.0 dated 28.02.2023
Source(s) of Monetary or Material Support	Grant: SNSF 33IC30_201300
Primary Sponsor	CHUV
Secondary Sponsor(s)	Not applicable
Contact for Public Queries	[name], [contact]
Contact for Scientific Queries	[name], [contact]
Public Title	Procalcitonin and Lung Ultrasonography Guided Antibiotherapy in Emergency Departments, The PLUS-IS-LESS study
Scientific Title	Procalcitonin and Lung UltraSonography based antibiotherapy in patients with Lower rESpiratory tract infection in Swiss Emergency Departments: a pragmatic stepped-wedge cluster-randomized trial
Countries of Recruitment	Switzerland
Health Condition(s) or Problem(s) Studied	Lower respiratory tract infections

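### Each center's training month falls inside its control period, contrary to the no-exposure statement, and any spill-over would favour the non-inferiority claim

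*Protocol article*

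**What the plan says.** The Discussion part of the abstract defends cluster randomization on the ground that "physicians are not exposed to the intervention during or before the control period". The main Discussion repeats this and adds that contamination would bias the trial toward the null.

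The Training section sets a timetable that begins "In the month prior to the intervention period". In that month "the medical supervisors (senior registrars and senior physicians) of the respective ED will attend a 1-h presentation on the scientific data behind the algorithm". The same people complete the lung ultrasound (LUS) e-learning, a theory hour and a practical session that includes pneumonia diagnosis on admitted patients. They then take a quiz and record two or five examinations, depending on previous expertise.

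Under Randomization, allocation, and timeline, one center switches "at each pre-determined time period (every 10 weeks, which corresponds to a step"). No transition period is named. The Control group section leaves antibiotic decisions and the choice of tests to the physicians.

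There is also a more general exposure. The Discussion reports that "we presented the rationale behind the algorithm during the site initiation visits", and the Monitoring section says "Site initiation visits were conducted on each site before the start of the trial".

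**The concern.** If the physicians who supervise an ED learn the algorithm's evidence and LUS while patients are still enrolled as usual care, the last control weeks may no longer be pure usual care. Nothing in the control condition stops a newly trained supervisor from using LUS or procalcitonin (PCT), or from prescribing differently.

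The direction of the bias matters because the two co-primary endpoints need opposite things. For antibiotics, dilution makes superiority harder to show, so the error is on the safe side. For clinical failure, dilution shrinks any true excess and so makes non-inferiority easier to declare. The affected weeks sit next to the switch, where the stepped-wedge model draws much of its within-cluster information.

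**Working it through.** **1. Is the training month control time?**
- "Recruitment started on December 5, 2022, and will be completed on November 3, 2024": counted inclusively this is 700 days, or 100 weeks.
- One baseline period plus nine steps of 10 weeks is 10 × 10 = 100 weeks, so no week is left for a gap.
- The sample size section counts every cluster-period in full, "leading to our final sample size of 1530 (17 × 9 × (9+1)) patients".

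Continued enrolment in that month is an inference, but the arithmetic leaves no room for a pause.

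**2. How many patients?** Center k has k control periods, so there are 1 + 2 + … + 9 = 45 control cells and 45 × 17 = 765 control patients. Four weeks are 40% of each center's last control cell: 9 × 17 × 0.4 = 61 enrolled (9 × 15 × 0.4 = 54 evaluable). 61/765 = 8% of controls and 61/1530 = 4% of all patients.

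**3. Reproducing the stated power.** Inputs from the Sample size section: 9 clusters, 10 periods, 15 evaluable per cell, failure 20% in both groups, margin 0.10, ICC 0.2, cv 0.3, one-sided α 0.05. The Hussey–Hughes variance is

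Var = Iσ²(σ² + Tτ²) / [(IU − W)σ² + (U² + ITU − TW − IV)τ²]

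- I = 9, T = 10, U = 45, W = V = 285.
- Taking 0.20 × 0.80 = 0.16 as within-cluster variance and 15/1.09 = 13.76 as the effective cell size (1 + cv² = 1.09), σ² = 0.16/13.76 = 0.01163.
- τ² = 0.2 × 0.16/0.8 = 0.04.
- Var = 9 × 0.01163 × 0.4116 / (120 × 0.01163 + 660 × 0.04) = 0.00155, so SE = 0.0394.
- Power = Φ(0.10/0.0394 − 1.645) = 81.5%. This variant needs 14.36 per cell, which rounds up to 15, so it matches the plan.

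**4. Dilution.** Let ρ be the share of the intervention effect already present in the training month. It is not in the documents and is assumed here. Each center's last control cell then carries 0.4ρ of the effect. In the generalized least squares fit the retained fraction is r ≈ 1 − 0.213ρ. The error rate at a true 10-point excess is Φ((0.10 − 0.10r)/0.0394 − 1.645).

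| ρ (assumed) | r | 15-point antibiotic reduction reads | one-sided error, clinical failure |
|---|---|---|---|
| 0 | 1.000 | 15.0 | 5.0% |
| 0.10 | 0.979 | 14.7 | 5.6% |
| 0.25 | 0.947 | 14.2 | 6.6% |
| 0.50 | 0.893 | 13.4 | 8.5% |

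With a calendar month (4.34 weeks), r is 0.977, 0.942 and 0.884, and the error is 5.6%, 6.7% and 8.8%. These figures use the risk-difference scale, whereas the planned model is logistic, so they are approximations.

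**5. Cost of leaving the month out.** With each center's last control cell at 60% of its size, safety power falls from 81.5% to 77.8%. About 16 evaluable patients per cell would restore 80%, against 15 planned.

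**The case against.** The best defence is that the no-exposure sentence concerns the intervention itself. That is management with the PLUS algorithm, whose recommendation reaches the physician through the eCRF, and only switched EDs use it. Training is preparation, and LUS certification has to precede use: training after the switch would put untrained weeks into the intervention arm. The Discussion makes its point against individual randomization, where one physician would manage both groups at once. That contrast survives. What does not survive is the absolute wording, since supervisors do meet the algorithm's evidence and one of its two tests during control time.

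Spill-over is also probably small. Only supervisors are named, and their training is spread over the month. A linear climb to 25% by the switch averages 12.5%, which keeps 97% of the effect and gives an error of 5.7%.

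The plan does have a sensitivity analysis on usual-care patients who received PCT or LUS, which covers the most direct route. It does not isolate the training weeks, nor does it capture prescribing changed by the presentation alone.

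Two stronger readings are tempting. A reader might infer that a truly inferior algorithm would pass because a diluted 10-point excess reads below 10. The rule uses the upper confidence bound, however: at ρ = 0.50 an estimate of 8.9 has a bound near 8.9 + 1.645 × 3.94 = 15.4 points and fails. The error rate is the relevant measure. A reader might also infer from the site initiation visits that the whole control arm is contaminated. The article does not say who attended them, and the calculation above does not address that exposure.

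**Conclusion.** The point holds as a conflict between a stated design property and a stated schedule, with a known direction of bias and a probably modest size. The conflict needs no assumption about spill-over. That the month is control time rests on the 100-week arithmetic and the 90 full cells. The rise in one-sided error from 5% to between 5.6% and 8.5% rests on an assumed spill-over of 10% to 50%, four training weeks, and the variance convention that reproduces the stated power. The documents show a risk of contamination, not that contamination occurs. They therefore do not support calling the control arm invalid or removing these patients from the primary analysis.

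**What to change.** 1. Reword the no-exposure statement in the abstract and the Discussion. It should say that supervising physicians are trained on the algorithm's evidence and on LUS in the last month of their center's control period, and that the rationale was presented at site initiation.
2. Keep the primary analysis as planned.
3. For both co-primary endpoints, pre-specify a supporting analysis that omits control patients enrolled in each center's training month, or models that month separately. Require its safety result to be consistent with the primary result before non-inferiority is claimed, and define consistency in advance.

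The cost is two reworded statements and one additional analysis per endpoint, based on enrolment dates and each center's switch date. The supporting analysis is somewhat less precise (safety power about 78% against 81.5%). Because that falls below the planned 80%, the exclusion should support the primary analysis and not replace it.

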### Endpoints

The primary safety endpoint is the proportion or patients with clinical failure by day 28. Clinical failure is defined as death from any cause, secondary intensive care unit (ICU) admission for any cause, secondary admission to hospital (excluding elective admission), hospital re-admission after index hospital discharge (excluding elective admission), or local complications due to the LRTI (empyema, lung abscess).

The primary efficacy endpoint is the proportion of patients prescribed an antibiotic by day 28. Table 4 summarizes the secondary and exploratory endpoints.

**Table 4 Tab4:** Study endpoints

Primary safety endpoint	
Proportion of patients with clinical failure by day 28, defined as: death from any cause, or secondary ICU admission for any cause, or secondary admission to hospital (excluding elective admission), or hospital re-admission after index hospital discharge (excluding elective admission), or ­ local complications due to the LRTI (empyema, lung abscess)	
Primary efficacy endpoint	
Proportion of patients prescribed an antibiotic by day 28.	
Secondary endpoints	
Number of points on the CAP symptom questionnaire as a surrogate marker of quality of life on days 7, 28, and 90 in each study group.	
Duration of ED stay in each study group.	
Rate and duration of hospitalization in each study group	
Proportion of patients prescribed an antibiotic for a new respiratory infection in each study group between days 28 and 90.	
Proportion of patients with antibiotic-related side effects and *C. difficile* infections in each study group.	
Identification of barriers and facilitators to the implementation of the algorithm with patients and ED physicians involved in the study.	
Quality-adjusted life years (QALYs), derived from responses to the EQ-5D questionnaire, in each group	
Measurement of the incremental cost-effectiveness ratio (ICER) of the intervention as compared to usual care.	
Advanced automatic LUS image analysis method using machine learning to assist in LUS diagnosis and risk stratification.	
Proportion of physician reaching proficiency in LUS image/video acquisition and interpretation after the training module.	
Sensitivity, specificity, and area under the ROC of physician “gestalt” and Van Vugt prediction score for CAP diagnosis.	
Exploratory endpoints	
Proportion of LRTIs patients with a documented bacterial, viral, and mixed infection.	
Nasopharyngeal microbiome in adult Swiss patients with LRTIs.	
Urinary metabolite changes during antibiotic treatment.	
Presence and expression levels of new generation host biomarkers and transcriptome signature according to etiology and severity of the LRTI	

## Methods: Assignment of interventions

### Randomization, allocation, and timeline

The unit of randomization will be the nine centers, representing the clusters. In accordance with the stepped wedge cluster randomization design, after a common baseline 10-week-period of usual care (all patients included in the control group), one center will switch to the intervention phase (patients included in the intervention group) at each pre-determined time period (every 10 weeks, which corresponds to a step). All study centers will be in the intervention period for the last 10 weeks of the study (Table 5). The total duration of the study will be 113 weeks, including the follow-ups. The sequence of rolling into intervention (from control period to intervention period) was randomly generated between study centers using the web-based randomizing program: random.org. The nature of the study intervention precludes randomization at the patients’ level. Indeed, the intervention is targeting the decision-making process of the clinician and might contaminate the usual care group in case of patients’ randomization. Figure 3 represents the CONSORT flow diagram of the PLUS-IS-LESS study following SPIRIT guidance.

**Table 5 Tab5:**
[figure not shown]
Stepped wedge roll out of the PLUS intervention by study center over time. Center 1: Cantonal Hospital of St Gallen, center 2: University Hospital of Lausanne, center 3: Hospital of Neuchâtel, center 4: University Hospital of Basel, Center 5: Cantonal Hospital of Lucerne, center 6 : Intercantonal Hospital of Broye, center 7: Hospital Riviera-Chablais, center 8: Cantonal Hospital of Baden, center 9: Cantonal Hospital Baselland & St Clarasspital Basel

**Fig. 3 Fig3:**
[figure not shown]
CONSORT flow diagram of the study. LRTI lower respiratory tract infection, PCT procalcitonin, AB antibiotic

### Blinding

Centers are randomly allocated to one cluster with pre-determined dates to switch from usual care (control group) to the intervention (intervention group). The assigned cluster was disclosed to the study centers in the month before initiating the study, as blinding is not feasible in this open-label trial. In this context, data analysts are not blinded either.

